#### Secondary Hypotheses and Outcome Measures

We hypothesize that with use of the DA the Decisional Conflict Scale score will decrease [30]; knowledge about NAST, using a custom-designed questionnaire, will increase; information and involvement preference will increase [31]; agreement between preferred and achieved decision control will be high, based on an adaptation of the Control Preferences Scale to include achieved control [14]; and the Control Preferences Scale score will increase [14]. Further, there will be no change in cost of health care delivery or in the 6-item State-Trait Anxiety Inventory score [32]. Fear of cancer progression will be unchanged while receiving neoadjuvant therapy [33]; the Decisional Regret score after chemotherapy and after surgery will be low [34]; fear of cancer recurrence score will be low [35]; distress thermometer score will decrease [36, 37]; satisfaction with decision score will be high [38]; and there will be no change in outcomes between those who decided to receive neoadjuvant chemotherapy with those who decided not to have neoadjuvant therapy.

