**Decision-making preference questionnaire**						
	Preferred	X	X			
	Actual		X			
Distress thermometer		X	X	X	X	X
Information and involvement preferences		X	X			
EQ-5D-5L (optional)		X	X	X	X	X
Knowledge of decision aid information			X			
Decision aid feedback			X			
Satisfaction with decision scale			X			
Fear of progression (FOP 12)			X	X	X	
Decision regret scale				X	X	X
Fear of Cancer Recurrence Inventory				X	X	X
Participant-reported pathology results (NAST only)						X

^a^Postchemotherapy, before surgery.

^b^Postsurgery, before adjuvant chemotherapy.

^c^12 months (+/- 1 month) after registration.

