### Statistical Analysis

A sample size of 50 participants is planned. The primary analysis will include all registered patients and clinicians as two separate cohorts. The proportion of patients and investigators who consider the DA acceptable will be reported with 95% exact confidence limits. The primary outcome will be considered positive if more than half of patients and clinicians consider the DA acceptable, and feasible if more than half of eligible patients who are offered participation register and subsequently use the DA. Assuming a sample size of 50 participants, the primary outcome of percentage of participants finding the DA acceptable can be estimated to within ±15% based on 95% exact confidence limits. To ensure that the lower 95% one-tailed exact confidence limit is greater than 50%, at least 32 of the 50 participants will need to indicate DA acceptability. Although the study is not powered to test the secondary hypotheses, there is 80% power to detect a change of at least 0.40 standard deviations from the pre- to post-DA assessments using a two-tailed *t*-test with alpha=.05 and a sample size of 50 participants.

Changes in secondary outcome measures from the pre-DA assessment, including decisional conflict, information preference, anxiety, distress, and fear of progression, will be evaluated using repeated measures analysis of covariance (ANCOVA). All outcomes will be described using mean and standard deviation for continuous measures and frequency for categorical outcomes. If data are skewed, median and interquartile range will be reported and the appropriate linearizing transformation will be used. Analyses will be performed unadjusted and adjusted for age, level of education, information preferences, and tumor characteristics (size, grade, node involvement, ER/PR/HER2). Agreement in decisional control before and after using the DA, and between preferred and actual control, will be assessed using a weighted kappa statistic with McNemar test. Knowledge will be reported as mean proportion of items correct with standard deviation. Cost will be recorded using Australian Medical Benefits Scheme item numbers and Pharmaceutical Benefits Scheme prices, and a comparison made between those who receive surgery first and those who receive systemic therapy first.

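### The hypothesised increase in the Control Preferences Scale score is matched only to weighted kappa with McNemar test, which say little about an ordered upward shift

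*Protocol article*

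**What the plan says.** The section Secondary Hypotheses and Outcome Measures states two separate expectations about decisional control. One concerns agreement: "agreement between preferred and achieved decision control will be high". The other concerns change: "and the Control Preferences Scale score will increase".

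Table 1, under "Decision-making preference questionnaire", collects preferred control before the aid and again after the treatment decision. Actual control is collected only after the decision. A pre-to-post change can therefore be measured for preferred control and for nothing else on this scale.

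The Statistical Analysis section covers both comparisons in one sentence: "Agreement in decisional control before and after using the DA, and between preferred and actual control, will be assessed using a weighted kappa". The full method is given as "weighted kappa statistic with McNemar test". No two-category cut and no multi-category version of McNemar is stated.

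A separate sentence assigns repeated measures ANCOVA to "Changes in secondary outcome measures from the pre-DA assessment, including decisional conflict, information preference, anxiety, distress, and fear of progression". Decisional control is not among the five outcomes listed. The same section says the study is not powered for the secondary hypotheses, but adds that "there is 80% power to detect a change of at least 0.40 standard deviations from the pre- to post-DA assessments", by a two-tailed t-test at alpha 0.05 with 50 participants.

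**The concern.** An increase is a statement about direction. Agreement is a statement about how closely two readings match. Weighted kappa answers the second question and suits the preferred-versus-achieved hypothesis. For the before-and-after comparison it leaves the stated hypothesis unanswered: a shift can occur and the headline statistic can still read as good agreement.

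McNemar is the only named element that could pick up a shift, and it works on two categories. Weighting in kappa has meaning only with three or more ordered categories, so the two statistics imply different forms of the same variable. To use McNemar in its usual form someone must choose a cut, and with none stated the choice could be made after the data are seen.

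At stake is one secondary hypothesis about involvement in the decision. This is not a detail left for later: the article names a method, and that method does not fit one of the two hypotheses it appears to serve.

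**Working it through.** **The plan's own figure.** The only stated figure on pre-post change is 80% power for 0.40 SD, two-tailed alpha 0.05, n = 50.
- Normal approximation: Φ(0.40 × √50 − 1.96) = Φ(2.828 − 1.960) = Φ(0.868) = 80.7%.
- Noncentral t, paired test: 79.2%.

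The figure reproduces to rounding. It applies to a t-test on a score change, not to kappa or McNemar.

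**Worked table.** The article gives no number of levels or distribution, so these are assumptions: five ordered levels, 10 patients at each level before the aid, 4 patients from each of levels 1 to 4 moving up one level, nobody moving down. Up means towards a higher score. The after-aid counts are 6, 10, 10, 10 and 14; 16 of 50 have moved.

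Weighted kappa = 1 − (observed mean disagreement) / (mean disagreement expected by chance).
- Observed: 16/50 = 0.32 for both weightings, since every move is one step.
- Expected, linear: mean distances to levels 1–5 from a uniform baseline are 2, 1.4, 1.2, 1.4, 2. Expected = 0.12×2 + 0.20×1.4 + 0.20×1.2 + 0.20×1.4 + 0.28×2 = 1.60. Kappa = 1 − 0.32/1.60 = 0.80.
- Expected, quadratic: mean squared distances are 6, 3, 2, 3, 6. Expected = 0.12×6 + 0.20×3 + 0.20×2 + 0.20×3 + 0.28×6 = 4.00. Kappa = 1 − 0.32/4.00 = 0.92.

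Direction: if the 16 all move down instead, or 8 move up and 8 down (2 each way across each boundary), the observed term stays 0.32 and the expected terms stay 1.60 and 4.00. Kappa is again 0.80 and 0.92. In this table it cannot separate the hypothesised result from its opposite or from no net change.

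Tests on the same table:

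| Method | Uses | Result |
|---|---|---|
| Exact McNemar, any single cut | 4 up, 0 down; 12 of 16 movers ignored | p = 2 × 0.5⁴ = 0.125 |
| Bowker (multi-category McNemar) | four pairs, each (4 − 0)²/4 = 4; total 16 | p = 0.10 on 10 df; 0.003 if only the 4 non-empty pairs count |
| Sign test | 16 up, 0 down | p = 2 × 0.5¹⁶ = 0.00003 |

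Because all non-zero changes here are the same size, an exact Wilcoxon signed-rank test gives the same p as the sign test.

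**A second table.** The baseline is uneven (8, 12, 15, 11, 4). From levels 1 to 4, the numbers moving up one level are 4, 4, 4 and 3; none move down. Kappa is 0.77 linear and 0.89 quadratic. Exact McNemar gives p = 0.125 at three cuts and 0.25 at the fourth. Bowker gives p = 0.13 on 10 df (0.005 on 4). Wilcoxon gives p = 0.0001.

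**Simulation.** Assumptions: n = 50, a latent bivariate normal cut into five levels (cumulative 10%, 35%, 70%, 90% at baseline), pre-post correlation 0.6 to 0.9, latent shift 0.40 SD of the change, 2,000 runs per setting. Unlike the tables, this allows downward moves.
- Paired t-test on the level scores: power 57% to 69%. This is below 80% because grouping into five levels shrinks the observed effect to 0.31–0.37 SD.
- McNemar at one cut (three cuts tried): 2% to 33%, depending on cut and correlation.
- Bowker, 10 df: 0.4% to 7%.
- Mean quadratic kappa, no shift versus shift: 0.54 to 0.51 (correlation 0.6), 0.73 to 0.71 (0.8), 0.83 to 0.82 (0.9).

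**The case against.** The strongest reply is that the article never says kappa tests the increase. The ANCOVA sentence on changes opens its list with *including*, the scale score is a secondary outcome, and power is framed as a t-test on change. On that reading, change goes to ANCOVA and agreement is extra description. The open list does leave that room, but it does not settle the matter: decisional control is absent from the five named outcomes, and the one sentence that names it before and after gives it a different method.

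Second, McNemar does test for a systematic shift once the scale is dichotomised, so the plan is not blind to one. That stands. What remains is the unstated cut and the lost information.

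Third, the illustration is favourable: equal flow across every boundary leaves only four movers at any cut, and no downward moves makes the sign test as strong as it can be. With six crossing and none returning, exact McNemar gives 2 × 0.5⁶ = 0.031. This also stands; the size of the loss rests on assumptions, though the simulation shows the same ordering without those two features.

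Some stronger inferences are tempting and should be resisted:
- *A high before/after kappa contradicts an increase.* It does not; the worked table has both together. Kappa is uninformative here.
- *McNemar and weighted kappa cannot be used on one table.* The Bowker form exists for several categories. Its weakness is that it tests symmetry, not direction.
- *McNemar should simply be removed.* For preferred versus actual control, a directional test can show whether patients had less control than they wanted, which kappa alone cannot.
- *The pre-aid preference must be the comparator for actual control.* Table 1 collects preference at both times, and the article does not say which is meant.

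**Conclusion.** The point holds in limited form. The article states a directional hypothesis about the Control Preferences Scale score and the data to test it will be collected, but the only method named for that comparison measures agreement, backed by a test that needs an unstated cut or, in its multi-category form, does not test direction.

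The mismatch does not depend on the illustrative numbers. Its size does: under the assumed five levels at n = 50, single-cut McNemar had 2% to 33% power where a paired test on the scores had 57% to 69%, and mean quadratic kappa changed by 0.01 to 0.03. The stated 80% power does not carry over to the named method.

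A reader might infer that the study cannot assess involvement at all. The documents do not support that: weighted kappa suits the preferred-versus-achieved hypothesis, and information preference is in the ANCOVA list. This is one secondary hypothesis in a study that says it is not powered for them, and the primary acceptability and feasibility outcomes are untouched. It is worth correcting because the correction is nearly free.

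**What to change.** - Test the pre-to-post change in preferred control with a paired ordinal test on the full scale, for example Wilcoxon signed-rank, and report the numbers moving up, moving down and unchanged.
- Keep weighted kappa with a 95% CI for preferred versus actual control. For that comparison, replace McNemar with the same paired ordinal test, or prespecify the cut, so that systematic under-involvement can still be seen.
- State which preferred value, before the aid or after the decision, is compared with actual control.

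The cost is a sentence or two of analysis wording and no new data. The article reports 29 of 50 participants registered, so the wording can be settled before analysis.

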#### Missing Data

Patients are encouraged to complete all questions but are not compelled to enter responses to any of the individual questions within each set of questionnaires and can submit responses with blank fields. Prior to questionnaire submission, patients will receive a prompt informing them that not all questions have been answered and to amend if they wish. During the study, levels of missing data are being monitored. If data completion rates drop below 70%, remedial action will be taken. An analysis of missing data will be completed at the end of the study.

## Results

The study is currently recruiting at four Australian centers. As of February 2016, 29 of the planned 50 participants have been registered to the study. Recruitment is expected to be complete in mid-2016, with early results available late 2016.

## Discussion

### Principal Considerations

This study intends to evaluate the acceptability and feasibility of a DA for women with operable breast cancer who have been offered NAST. It is designed as a single arm pre-post study to allow all participants access to the intervention. The population of Australian women who currently receives NAST is relatively small, limiting the feasibility of a larger, randomized controlled trial with comparative outcomes. However, the proportion of patients receiving NAST in Australia and New Zealand is expected to increase as a result of increased awareness, availability of neoadjuvant clinical trials, and from the results of ongoing neoadjuvant and post-neoadjuvant trials.

The study primary endpoints are pragmatic. We expect that some participants will not find the DA beneficial, based on their decision-making style and information-seeking behavior. However, we hypothesize that the number who find it helpful in their decision-making process will be greater than the number who do not find it useful. Because DAs have variable use across centers and individual clinicians [40], feasibility was included as an endpoint. A screening log is designed to quantify the number of patients who are seen at recruiting sites who are candidates for NAST for operable breast cancer; are eligible for the study; are offered study participation; accept study participation; and go on to access the DA. This will identify the proportion of eligible patients who are not offered participation (clinician feasibility) and the proportion of eligible patients who do not access the DA after being offered it (patient feasibility). Acceptability will be assessed using direct questions to patients and clinicians.

Outcome measures were selected based on the availability of valid, reliable questionnaires that assess outcomes relevant to decision making in the context of a decision aid. In a systematic review of the quality of measures to test the effectiveness of decision support strategies, the Decisional Conflict Scale and the Control Preferences Scale satisfied the largest number of quality criteria [41]. These are commonly used measures of DA effectiveness [21, 42]. Knowledge assessment necessitates a custom-designed questionnaire. The Fear of Progression questionnaire is suited to the neoadjuvant setting where the primary cancer is present and has the potential to impact on psychological and physical domains [33]. The Information and Involvement Preferences questionnaire was included to determine the information needs of patients and to correlate the result with patient and clinician acceptability. The EQ-5D-5L is a health economic utility measure [43] and was included as an optional measure to determine patients’ willingness to complete this additional questionnaire. If patients are willing to complete it, then it will be considered for future comparative studies as a health economic measure. Satisfaction with decision is of interest as an acute measure to be assessed after the decision has been made, but prior to experiencing the consequences of the decision [34]. Decision regret is a longer-term outcome measure, to be assessed after the consequences of the decision have been experienced [38].

Increased anxiety is associated with both more effective decision strategies and stressful health interventions, so is not a good measure of the benefit of DA use [44]. Anxiety therefore is not expected to decrease as a result of a DA, but nor should it increase and therefore anxiety has been included as a safety measure [21].

Decision aids are most beneficial if endorsed by a clinician at the time they are offered to the patient and referred to after the decision has been made [45]. This decision aid is introduced at a time when patients have recently been diagnosed with breast cancer and are faced with a number of complex decisions that are influenced by a variety of sources including clinicians, family, and the media [46, 47]. Patients are identified as suitable for the decision aid by their doctor (usually a surgeon) and are generally referred to a medical oncologist to discuss systemic therapy. The decision aid is suited to this situation as there is often a period of several days (or more) before an available appointment with a medical oncologist. If the decision aid is effective, the patient will be more prepared to be involved in the decision when they come to the medical oncologist. Balancing the provision of complex information with adequate readability proved difficult, as demonstrated by a higher Flesch-Kincaid grade than would be ideal.

Decision aids have been shown to have a variable effect on treatment choices [21]. For selected treatment decisions, some patients change their preferred treatment after a DA, but for others decision aids have been shown to have a neutral effect. We anticipate that study patients will not change their decisions after accessing the DA, as decisions such as this tend to be made based on a number of information sources [48].

If shown to be feasible and acceptable, the DOMINO decision aid has the potential to be offered to patients as part of routine clinical practice. There is good evidence for the efficacy of decision aids that are designed according to international standards [22,24]. Thus, a randomized controlled trial is not considered a prerequisite for dissemination. Clinicians who enroll participants in this study will be asked whether they would continue to use the decision aid as part of routine practice, as an indicator of perceived implementability.

### Conclusion

Use of the DOMINO decision aid has the potential to decrease decisional conflict, increase knowledge, and increase patient involvement in women who have been offered NAST. Increased involvement in decisions by women with breast cancer is associated with improved decision-related outcomes [18] and long-term quality of life [19]. Neoadjuvant clinical trials are an established drug development pathway, and the decision aid may allow better understanding of the rationale behind neoadjuvant therapy. The patient may then be able to be better informed about the trial. It may also assist clinicians who are introducing neoadjuvant systemic therapy into their practice but have not yet become confident addressing the concept with their patients.

## Abbreviations

DA: decision aid
ER: estrogen receptor
EQ-5D-5L: EuroQol 5-dimension, 5-level health status measure
HER2: human epidermal growth receptor 2
NAST: neoadjuvant systemic therapy
PR: progesterone receptor
